### Research question

Is probiotic (Vivomax) use as prophylaxis a cost-effective strategy for preventing sepsis among 0–2-month-old infant population in India?

Objectives: to assess the cost utility of using probiotics as prophylaxis for sepsis among LBW neonates of age 0–2 months.

### Study methodology

A cost utility analysis (CUA) is proposed to be conducted alongside the multicentre RCT. Randomised controlled trials (RCT) are considered the ‘gold standard’ as they produce a reliable the best evidence of treatment effect. The economic evaluation alongside RCT provides opportunity to collect data both on disease-specific disability and resource use. Start date is 15 November 2022 and the anticipated completion date is December 2023.

### Model overview

#### General description

This protocol describes the methodology for economic evaluation within a phase III RCT—the ProSPoNS trial. The details are described in the following sections.

#### Decision model

In view of the shortcomings of treatment effect measure coming from a single RCT, we also propose using a model-based approach which will allow synthesising information from all sources for a health technology enabling us to explore scenarios not explicitly found in the trial data. Moreover, the modelling approach would enable to estimate the long-term benefits of intervention incorporating quality of life measures. Furthermore, it allows accounting for uncertainties present in assumptions and data used for economic evaluation, which has implications for policy question under consideration. The clinical outcomes from trial would be sepsis episodes averted as an effect of probiotics use in the intervention arm. Quality of life (QUALY) is a preferred utility measure for economic analysis; however, there is no EQ-5D version for neonates. Therefore, in order to assess the long-term effects, we propose to use ‘DALY’ as the measure of health outcome, which accounts for both disability and quality of life. A decision-analytic model following a systematic approach in bringing together evidence on clinical effectiveness, health-related disability of life and costs associated with the probiotic intervention as compared with placebo will be used with the aim to provide information on whether the reduction in neonatal sepsis incidence justifies the incremental costs. Figure 2 depicts the decision model for the proposed study.

**Figure 2 F2:**
[figure not shown]
Decision tree for cost-effectiveness of using probiotics as prophylaxis for sepsis among neonates of age 0 to 2 months.

#### Outcome measures

Primary outcome measure for economic evaluation (within-trial CUA) would be sepsis episodes and related deaths averted in the intervention arm as compared with the placebo arm, which translates to gain in life years and DALYs averted as long-term measure.

Data requirements: data requirements for economic evaluation are tabulated in table 1.

**Table 1 T1:** Data requirements for economic evaluation

Data type	Significance for the model	Source of data
Demographic	Estimate the baseline parameters Estimate target population	Primary data collection; Census of India
Treatment effects and incidence of adverse events	Efficacy and safety parameters Cost estimation Outcome assessment	RCT Database
Background mortality data	Estimate natural mortality in the target population	SRS, Published literature
Utilities	Estimate DALY as long-term outcome measure	Global Burden of Diseases estimates (2011)
Resource use and price data	Cost estimation	Primary data collection; NHSC—Prinja *et al*
Epidemiological data	Estimate baseline risk of clinical events	Published literature; Primary data collection (Control arm of the RCT)

NHSCD, National Health Systems Costing Database; RCT, randomised control trial; SRS, Sample Registration System.

Utility data would allow incorporating the relative impact of a health technology (ie, probiotics) on the neonatal health outcomes in terms of disability burden. This will be estimated as DALYs averted. Utility data would be obtained from Global disease burden estimates 2017. Cost data are important drivers of cost-effectiveness, as they quantify the resource consumption associated with the use of health technologies.

Decision-analytic model would be populated with cost data from the societal perspective: direct medical and non-medical cost borne by patients; and direct medical cost borne by the healthcare system. A National Health Systems Costing Database (NHSCD) to estimate healthcare system’s costs in India has been developed.^12^ Data on patient’s out-of-pocket (OOP) expenses would be collected during the conduct of the RCT as primary data.

A health economic evaluation using CUA design will be conducted within the ProSPoNS trial. The results would provide the incremental costs and health gains of the probiotic intervention in absence of any prevention modality being implemented or available. Decision-analytical modelling using the trial results would be extrapolated to the target population and time horizon to inform policy on the potential for incremental costs offsets attributable to prevention of morbidity with the proposed intervention. The CUA will use the present results as cost per case of neonatal sepsis prevented. CUA will present the results as cost per DALY averted. Intervention costs and effects will be extrapolated to the Indian neonatal population. Modelling will be used for the target population, time horizon and the decision context to provide much required information for the policymakers. It would guide further decision for upscaling the intervention, if it is found to be efficacious. If the incremental costs of the intervention can be offset by the gains in terms of effectiveness (ie, DALYs), it may be presented for induction within the ambit of existing governmental programme. Modelled CUA results can be presented as health-adjusted life years saved and savings of the healthcare system by disease prevention. We will calculate the incremental cost-effectiveness ratios as the difference in the costs between the intervention and the comparator divided by the difference in health outcomes.

### Effectiveness assessment

Prevention of severe sepsis in the early neonates will prevent the long-term morbidity like neurodevelopmental disability risk associated with sepsis^13^ and reduce mortality due to pneumonia, meningitis and neonatal sepsis and hospital admissions due to any infectious diseases.^14^

We propose to use the short time horizon to assess the sepsis averted as a result of probiotics supplementation for 1 month and model the change in DALYs in the intervention group as a long-term measure.

### Study details

Total of 6144 (N) new born babies with LBW would be screened for eligibility and randomly assigned to probiotic (n=3072) or placebo (n=3072) groups and administered 1 mL of the probiotic suspension daily for 30 days. The study would use Interactive Web Respons System (IWRS) for the purpose of stratified randomisation by birth weight, sex and study site. Trained field workers will make home visits daily for first 7 days and thereafter three times in a week till day 30 of the follow-up period to ensure and monitor adherence to the intervention and collect morbidity information. After the 30-day intervention period, home visitation will continue at weekly interval till day 60 of life. During home visitation as per schedule, trained fieldworkers would screen infants for symptoms/signs of possible serious bacterial infection (PSBI)/clinical illness/clinical severe infection. To record the adverse event (AE)/serious adverse event (SAE) (if any), continuous monitoring and reporting of ongoing medical conditions, signs and symptoms will be conducted by field worker during their scheduled follow-up home visits using software on handheld device during the 2-month period of follow-up. Presence of any danger signs would be evaluated, and need for referral would be assessed: if a child is found to have any symptoms/signs from the list, the field worker will accompany the infant to facility for examination by study physician (referral). The study physician would examine the infant again for symptoms/signs of PSBI/clinical illness/clinical severe infection and confirm the diagnosis. Investigations such as blood culture, sepsis screen would be performed for suspected cases of neonatal sepsis by study physician. If required, the infant would be hospitalised for treatment. Data on outcomes, lab investigation and treatment during clinical management of the sick, new born will be collected and SAEs will be reported as per regulatory guidelines. Blood culture isolates will be shipped by site to microbiology lab at All India Institute of Medical Sciences, New Delhi for quality assurance purpose.

The study will be implemented according to MRC guidelines for management of global health trials and will be governed by a Trial Steering Committee and a Data Management Committee.

#### Primary outcomes

*1. Sepsis:* defined as one or more clinical symptoms suggestive of sepsis with a microbial isolate on blood culture; or a neonate with sterile blood culture with at least 2 sepsis screen markers being abnormal (absolute neutrophil count <1500/mm^3^; Total Leucocyte Count (TLC) <5000/mm^3^; immature to total neutrophil ratio >0.2; immature to total neutrophil ratio >0.2; C reactive protein (CRP) >1.2 mg/dL, ESR >15 mm).*2. PSBI:* one or more clinical signs like fever (temperature ≥38°C), low body temperature (< 35.5°C), not feeding well, convulsions, fast breathing (60 bpm or more), severe chest in-drawing, movement only when stimulated or no movement at all in infants less than 7 days old confirmed by study physician.

#### Secondary outcomes

*1. Clinical severe infection:* one or more clinical signs like severe chest in-drawing, not feeding well, fever (temperature ≥38°C), the movement only when stimulated as confirmed by the study physician, low body temperature (< 35.5°C).*2. Critical illness:* one or more of clinical signs like unable to feed at all, unable to cry, no movement on stimulation, bulging fontanelle, cyanosis as confirmed by the study physician and convulsions. The flowchart below (figure 1) depicts the study design and the study processes that will be followed during the implementation of the proposed research work (diagram, to be finalised after finalisation of methods). Primary and secondary outcomes would be compared between the two study arms to assess clinical effectiveness of probiotic intervention.

### Costing

In the current study, cost of Vivomix (intervention), cost of routine home-based postnatal care, cost of illness management, drug costs, vitamin/mineral supplement costs, laboratory investigation charges, doctor consultation and bed charges are categorised as direct medical costs and the informal payments and travel are categorised as the direct non-medical costs. Loss of wages of parents and other caregivers due to absenteeism from work and is categorised as indirect costs. Neonatal sepsis episodes are treated in in-patient (IP) setting; therefore, respondents (parents and caregivers) will be interviewed to collect information on days they were absent from work due to hospital stay for treatment. After hospital discharge, follow-up with parents and caregivers to assess any effect on their productivity at work is beyond the scope of data collection in the present study. All costs related data would be collected from all six study sites in a representative manner.

*Sample size (costing):* we calculated the sample size to estimate the mean OOP expenditures among the neonates with illness (here PSBI). A power of 80% and 5% level of significance was assumed for sample size calculation. The baseline estimate for OOP among neonates with PSBI was accessed from an Indian study.^1^ Assuming a mean OOP of ₹2003 (SD: ₹3517) for neonates with PSBI and an error margin of 7.5%, the minimum sample size computed to estimate the OOP was 1998. In view of high variability in the OOP data, the error margin of 7.5% was considered appropriate for sample size calculation. The data on OOP will be captured for a subsample, that is, 1998 neonates, out of total sample recruited in the study. At each of the six subjects’ recruitment sites, data would be collected on 333 subjects for this substudy. The OOP data will be collected irrespective of status of neonates belonging to two study arms. The formula used for sample size calculation is given below: n=Z21_1-a/2_ s2 d^2^

$$n=\frac{Z_{1-a}^{2}/2S^{2}}{d^{2}}$$

Where

n=minimum estimated sample size.

Z^2^_1-a_= table value from standard normal distribution.

s^2^=SD of outcome variable in study population.

d^2 =^ error margin (or absolute precision).

*Data collection and estimation of costs:* data collection for the current study would be completed in 1 year duration from September 2022 to August 2023 (to cover any variation with seasonality). Data on OOP expenditures will be collected on a subsample of 333 subjects drawn from the total trial population in a representative manner.

Sociodemographic data on education, occupation of parents of enrolled children is being collected on study forms. Parents would be asked about any illness during the study period and any expenditures on account of care seeking, visits to facilities, hospitalisation and treatment. Direct medical and non-medical costs due to neonatal sepsis would be ascertained in all 333 subjects at the six study sites. Data on OOP expenditure in public or private health facilities would be elicited.

Intervention cost would be facilitated through primary data collection and the programme budgetary records. The cost of treatment for neonatal sepsis and related diseases at secondary and tertiary level will be ascertained from the NHSCD^15 16^ and published literature in Indian context.^12^ These sources provide estimates on cost per IP admission, cost of intensive care unit admission, cost per out-patient consultation accounting for resources consumed for service provision such as medical (drugs, diagnostics, procedural, hospital charges) and non-medical (transportation, boarding and lodging). In addition, cost related to Information Education and Communication (IEC) material, monitoring and supervision and other administrative costs will also be estimated. Assumptions made in the study protocol are provided in table 2.

**Table 2 T2:** Key methods and assumptions for economic evaluation

Component	Consideration/approach	Justification
Intervention	Vivomixx (eight strain probiotics) + sepsis management Dose: 1 mL/day (10 billion CFU/mL) for 30 days Intervention delivery: under the supervision of study staff (field worker)	Effectiveness of Vivomixx for preventing neonatal sepsis is being assessed under trial
Comparator	Placebo	Effectiveness of Vivomixx is being assessed under trial against placebo Use of antibiotic is routine practice for sepsis management.
Target population	High-risk LBW neonates (both pre-term and small for-date babies)	Most vulnerable high-risk population with high morbidity and mortality
Objective	To assess the incremental cost per DALY averted with use of probiotics for prevention of neonatal sepsis compared the placebo	Besides effectiveness, evidence on cost-effectiveness is mandatory for adoption of treatment/intervention under public policy
Target Audience/policy use	National Health Mission (NHM) Any other	This intervention is to be implemented under RMNCH programme
Method	Both model and trial based	Short –term outcome estimates will be used for trial Use of model-based CEA will enable us to assess long-term outcomes (and sub-group analysis)
Perspective	Societal perspective	OOP burden associated with sepsis management among LBW neonates
Analytic horizon	6 months	To model long-term outcomes (DALYs)
Costs	Health system costs (Vivomixx cost; Cost of routine HBPNC care; cost of illness management etc.) OOP expenditures (doctor’s consultation; bed charges; drug costs; vitamin/mineral supplement costs; investigations; procedures; informal payments; travel cost etc.	Both health system and patients’ costs as per societal perspective considered for CEA
Outcomes	Sepsis episodes and deaths averted DALYs Hospitalisation averted Life years gained	In line with study design (cost-effectiveness/cost-utility analysis)
Discount rate	3%	As per Indian reference case

CEA, Cost Effectiveness Analysis; DALYs, disability-adjusted life years; HBPNC, home-based postnatal care; LBW, low-birth weight; OOP, out-of-pocket.

Total cost will be comprised of cost of intervention, cost of management of sepsis and associated complications and patient costs as OOP. Similarly, total cost in the control arm will be estimated in the absence of intervention. Annual discount rate of 3% will be used wherever applicable. In the present study, both model-based approach as well as trial data would be used. Data management and analysis will be done using MS-Excel.

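### The out-of-pocket (OOP) cost sample of 1998 is calculated as a number of PSBI cases but filled with infants drawn from the whole trial, so the stated 7.5% margin cannot be reached

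*Protocol article*

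**What the plan says.** All of this is in the protocol article, Costing section.

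- **Target of the calculation** (paragraph on sample size): "we calculated the sample size to estimate the mean OOP expenditures among the neonates with illness (here PSBI".
- **Error rates:** "A power of 80% and 5% level of significance was assumed for sample size calculation".
- **Inputs:** "Assuming a mean OOP of ₹2003 (SD: ₹3517) for neonates with PSBI and an error margin of 7.5" per cent.
- **Result:** "the minimum sample size computed to estimate the OOP was 1998".
- **Who fills the sample:** "The data on OOP will be captured for a subsample, that is, 1998 neonates, out of total sample recruited in the study", and "At each of the six subjects’ recruitment sites, data would be collected on 333 subjects for this substudy".
- **Sampling frame** (paragraph on data collection): the subsample is "drawn from the total trial population in a representative manner".
- **When illness is established** (same paragraph): "Parents would be asked about any illness during the study period". Illness is an answer at interview and not a condition of entry.

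No sentence limits the subsample to infants with PSBI or enlarges it for the share who do not fall ill.

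**The concern.** A sample size computed from the mean and SD of ill neonates counts ill neonates. If it is filled from all enrolled infants, only the fraction with PSBI informs the quantity that was sized. Well infants carry information on routine-care spending but none on the mean OOP of a PSBI case.

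Table 2 justifies the societal perspective by the OOP burden of managing sepsis, and patient OOP is part of total cost. Health-system treatment costs come from an existing national database, so patient OOP is the cost component that rests on this primary data collection. The uncertainty analysis assigns cost parameters a gamma distribution and reports a 95% interval for the ICER. A precision claim that the design cannot meet would mislead readers about how well this input is known.

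**Working it through.** **Inputs.** Mean 2003, SD 3517, relative margin 7.5% and n = 1998 (Costing, sample size). Trial size is 6144 (Background; Study details). The significance level is 5%; the in-line formula has Z at 1−a/2, so I take it as two-sided, z = 1.96. The proportion p of enrolled infants with PSBI is not given and is varied as an assumption.

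**Step 1: the plan's own figure.** The absolute margin is d = 0.075 × 2003 = 150.2.

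n = (z × SD / d)² = (1.96 × 3517 / 150.225)² = 2105.6, so 2106.

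This is not 1998. Other readings do not give 1998 either:
- one-sided z: 1483
- adding a term for 80% power: 4302 two-sided, 3389 one-sided
- the displayed formula taken literally, with Z²/2: 1053 with two-sided z
- z = 2: 2193
- finite population correction with N = 6144: 1569

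A margin of 7.7% does give it: (1.96 × 3517 / (0.077 × 2003))² = 1997.6, so 1998. The 80% power has no place in the precision formula shown.

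**Step 2: best case, all 1998 with PSBI.** Margin = 1.96 × 3517 / (2003 × √1998) = 7.7%.

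**Step 3: the sample as drawn.** The expected number with PSBI is 1998p, so

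margin = 1.96 × 3517 / (2003 × √(1998p)) = 7.7% / √p.

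Relative to 1998 PSBI cases, the standard error grows by 1/√p.

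| Assumed p | PSBI infants among 1998 | Margin (% of mean) | SE inflation 1/√p | Infants to sample for 2106 cases (2106/p) |
|---|---|---|---|---|
| 5% | 100 | 34.4 | 4.5 | 42,120 |
| 10% | 200 | 24.3 | 3.2 | 21,060 |
| 20% | 400 | 17.2 | 2.2 | 10,530 |
| 30% | 599 | 14.1 | 1.8 | 7,020 |
| 50% | 999 | 10.9 | 1.4 | 4,212 |

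**Step 4: could the trial supply the cases?** Taking all 6144 infants, 2106 cases need p of at least 2106/6144 = 34.3%; 1998 cases need 1998/6144 = 32.5%. The costing window is one year, so the pool may be smaller.

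**Step 5: does a different target rescue the margin?** Suppose the aim were mean OOP per enrolled infant, with nothing spent by infants without PSBI (assumption). The mean is 2003p and the variance is p(3517² + 2003²) − (2003p)².
- p = 10%: SD 1264, mean 200.3, margin 1.96 × 1264 / (√1998 × 200.3) = 27.7%.
- p = 50%: SD 2681, mean 1001.5, margin 11.7%.

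Neither reaches 7.5%.

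**The case against.** **The subsample may be meant to consist of ill infants.** The protocol never says in so many words that infants of any health status are taken. The sentence on collecting OOP irrespective of status concerns study arm and proves nothing either way. The data-collection paragraph also says that costs due to neonatal sepsis will be ascertained in all 333 subjects, which can be read as a sample of sick infants. That leaves the text inconsistent, but it does not outweigh an explicit representative frame with illness asked about afterwards. On that reading the margin would still be 7.7%, and about a third of all 6144 infants would have to be cases.

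**333 or 1998?** The data-collection paragraph speaks of a subsample of 333. Read as 333 per site it agrees with 1998 (6 × 333), and I have used that. If 333 were the total, the margin would be 18.9% even with every infant ill.

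**The size rests on an assumed p.** This stands. PSBI needs only one or more of the listed signs, so a high proportion cannot be excluded. A reader might infer that the standard error will be several times larger than planned; that fits 5% or 10%, but at 30% it is 1.8-fold and at 50% 1.4-fold. A reader might also infer that most interviews go to infants with no illness cost. That is not shown, since parents are asked about any illness and not only PSBI.

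**The representative subsample has a use.** This stands too. Total cost by arm includes routine postnatal care, supplements and other illness. Collecting from PSBI cases alone would lose these, so the documents do not support dropping the subsample.

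**This is lost precision, not bias, on one input.** Agreed. The uncertainty section varies parameters over a plausible range and does not say that the subsample's standard error sets the gamma distribution. The effect on the ICER interval therefore cannot be quantified from the document.

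**Conclusion.** The point holds. The target population of the calculation (neonates with PSBI) and the frame used to fill it (all enrolled infants) do not match, and the stated 7.5% margin is not reached. With the stated mean and SD and a two-sided 5% level this is true at every PSBI proportion, since 100% already gives 7.7%. How far it is missed depends on p, which the document does not give: from about 34% of the mean at 5% PSBI to about 11% at 50%.

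One tempting inference should not be drawn: that taking every PSBI case would improve the margin by a fixed amount, say from 24% to 14% at 10% PSBI. The 14% counts about 614 cases from all 6144 infants, whereas OOP data are collected over one year and enrolment within that year is not stated. If half the infants fell in the window (assumption), 10% PSBI would give about 307 cases and 19.6%. If about 2000 did, the margin would be about 24%, as under the current design. Within one and the same pool of infants, taking every case yields at least as many cases as a representative subsample of it; nothing more specific can be claimed.

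**What to change.** 1. **Margin.** Replace 7.5% with the margin expected from the projected number of PSBI cases in the costing window. State the assumed PSBI proportion and the expected enrolment in that window, with a range. Correct the arithmetic (7.5% needs 2106 cases; 1998 cases give 7.7%) and remove the reference to power, which the calculation does not use.
2. **Trigger for the form.** Collect the OOP form from every infant at all six sites with physician-confirmed PSBI or sepsis arising in the costing window. Field workers already screen at home visits and accompany infants with signs to the study physician (Study details), so the pathway exists.
3. **Representative subsample.** Keep one for routine-care and other-illness spending, give it its own size, and state plainly whether 333 is per site.
4. **Analysis.** Treat OOP per PSBI or sepsis case and routine or other-illness OOP per infant as separate parameters. Pooling the two sources would over-represent ill infants.

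The cost is revised protocol wording, a changed trigger for an existing form, and a stated margin that looks less favourable. Whether the total number of interviews rises or falls depends on the PSBI proportion, enrolment in the window and the size chosen for the retained subsample.

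### The out-of-pocket sample size of 1998 does not follow from its inputs (they give 2106), the 80% power plays no part in it, and a later sentence gives 333

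*Protocol article*

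**What the plan says.** The protocol article's Costing section, under the run-in heading on sample size, sets out to estimate mean out-of-pocket (OOP) expenditure in neonates with PSBI. It gives these elements:

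- Error rates: "A power of 80% and 5% level of significance was assumed for sample size calculation".
- Inputs: "Assuming a mean OOP of ₹2003 (SD: ₹3517) for neonates with PSBI".
- Result: "an error margin of 7.5%, the minimum sample size computed to estimate the OOP was 1998".
- Formula: a one-sample precision formula in z, the SD and the margin d, and nothing else.
- Allocation: 1998 neonates out of all those recruited. "At each of the six subjects’ recruitment sites, data would be collected on 333 subjects for this substudy".

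The next paragraph of the same section, on data collection and estimation of costs, says: "Data on OOP expenditures will be collected on a subsample of 333 subjects drawn from the total trial population". A little further on, direct costs "would be ascertained in all 333 subjects at the six study sites".

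**The concern.** All inputs to the calculation are printed, so the result can be checked, and it does not come out. Either the margin or the sample size is misreported. The text also defends 7.5% as appropriate given the variability of the data, so the margin is meant as a design choice.

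Two further statements do not fit. Power is quoted for a calculation that tests nothing. The number of families to be interviewed also differs by a factor of six between two adjoining paragraphs, and the smaller number stands in the paragraph that describes the data collection.

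OOP expenditure is part of total cost under the societal perspective and so feeds the incremental cost-effectiveness ratio. A reader will take the printed margin as the precision of that input.

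**Working it through.** **Inputs**, all from the Costing section: mean ₹2003, SD s = ₹3517, margin 7.5%, significance level 5%. The in-line formula carries the subscript 1-a/2, so the interval is two-sided and z = 1.96. The margin is read as a percentage of the mean, so d = 0.075 × 2003 = ₹150.225.

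**1. The plan's own figure.** n = (z s / d)² = (1.96 × 3517 / 150.225)² = (6893.32 / 150.225)² = 2105.6, so 2106. The plan states 1998, which is 108 fewer (108/2106 = 5.1%).

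**2. Can 1998 be recovered?** These variants were tried:

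| Variant | n |
|---|---|
| d rounded to ₹150 | 2112 |
| z = 2 | 2193 |
| One-sided z = 1.645 | 1483 |
| Finite-population correction, N = 6144 | 1569 |
| d as 7.5% of the SD | 683 |
| 7.5% as the full interval width | 8423 |
| 80% power added, one sample, two-sided | 4302 |
| 80% power added, two samples, per arm | 8604 |
| Margin 7.7% in place of 7.5% | 1998 |

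Only the last row matches: d = 0.077 × 2003 = ₹154.2 gives 1997.55, rounded up to 1998. The likely explanation is a 7.7% margin printed as 7.5%.

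**3. Margin actually delivered.** Margin = z s / √n.

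- n = 1998: 6893.32 / 44.70 = ₹154.2, and 154.2 / 2003 = 7.70%.
- n = 333: 6893.32 / 18.25 = ₹377.7, and 377.7 / 2003 = 18.9%.

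**4. Power.** The formula has no term for it. Including it would have required at least 4302 (two-sided), so it did not produce 1998.

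**5. 333 against 1998.** 6 × 333 = 1998, so the sample-size paragraph agrees with itself. The data-collection paragraph gives 333 from the total trial population.

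**6. Who contributes to the mean.** The mean and SD are for neonates with PSBI, but the 1998 are taken from all recruited infants. Only those who fall ill inform this mean. The document gives no PSBI rate, so the rates below are assumptions:

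| Assumed PSBI rate | Ill infants among 1998 | Margin |
|---|---|---|
| 10% | 200 | 24.3% |
| 20% | 400 | 17.2% |
| 30% | 599 | 14.1% |

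**The case against.** The strongest reply is that little turns on the arithmetic. A margin of ₹154 in place of ₹150 on a mean of ₹2003 would not visibly move a cost-effectiveness ratio, and cost uncertainty is to be handled by probabilistic sensitivity analysis with gamma distributions. That stands as to size, but the printed n and margin still do not belong together.

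Three stronger readings are tempting, and the document does not support them.

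- *The substudy has been cut to 333 infants.* The sample-size paragraph is explicit about 333 at each of six sites, and the product is exactly 1998. The phrase about drawing from the total trial population occurs once. The second mention, of all 333 at the six sites, can be read as per site. A dropped 'per site' is the likeliest cause, and the 18.9% margin describes only the literal reading.
- *A between-arm comparison of OOP cost is claimed to be powered.* The stated aim is to estimate a mean, and data are collected without regard to arm. The power statement is superfluous; it is not a claim about a test.
- *The displayed equation halves Z squared.* It looks that way, but the in-line version puts the /2 in the subscript 1-a/2. This is a typesetting or extraction slip and not an error in the plan.

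A further objection is right and changes the remedy. Simply printing 7.7% beside 1998 would itself mislead, because most of the 1998 may never have PSBI.

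**Conclusion.** The point holds. On the stated inputs the required number is 2106, and 1998 delivers 7.70%. The 80% power plays no part. The sentence giving 333 from the total trial population conflicts with 1998 and has to be reconciled with it. The first two are small in effect, and the third is probably a wording slip.

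The larger consequence is conditional. Neither 7.5% nor 7.7% applies unless every sampled infant has PSBI and contributes OOP data. On an assumed PSBI rate of 10% to 30% the margin is about 24% to 14%, two to three times the printed figure. That range rests on the assumed rates and on the plan's own mean and SD. It is not a figure from the document.

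This concerns the precision of one cost input and does not touch the trial's clinical analysis.

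**What to change.** 1. Restate the precision: 1998 neonates with PSBI give a 95% margin of 7.7% of the mean (₹154), and this applies only if all 1998 contribute illness-related OOP data.
2. Because the subsample comes from all recruited infants, state the expected number with PSBI, the source of that rate, and the margin for that number.
3. Delete the 80% power statement.
4. In the data-collection paragraph, write *333 subjects per site (1998 in total)* at both mentions of 333.

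These are wording changes plus one added figure, the expected PSBI rate. Raising the number to 2106 (351 per site, 18 more at each) would match the printed 7.5% on paper. It would achieve that margin only if all 2106 had PSBI, so restating the margin is the better course.
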